### Measures

#### Overview

Assessments for the acquisition phase included self-report questionnaires administered at the enrollment call, and 3 months and 6 months later. Measures included demographics, self-reported weight and height, and the NCI FVS. Additional measures were added to the maintenance phase (RCT) to more accurately estimate F&V outcomes and to examine change in theoretical constructs from SCT and GST. Baseline (randomization), 6 months, and 24 months were considered the primary time points for the RCT. Assessments at 12 and 18 months post baseline were considered secondary. A subsample of participants who were eligible for the RCT were randomly selected and invited to have a blood draw at baseline (randomization) to assess serum carotenoids. Other than the in-person blood draw, all assessments were completed over the telephone by survey research staff who were blinded to condition.

#### Fruit and Vegetable Intake

The primary outcome measure was F&V, and it was assessed two ways: brief screeners and 24-hour dietary recalls. The NCI FVS [35] was considered the primary screener and was administered at all assessment time points. The screener assesses self-reported frequency of consumption in the last month and the portion size for 10 items that included 100% fruit juice, fruit, lettuce salad, french fries or fried potatoes, white potatoes (not fried), cooked dried beans, other vegetables, tomato sauce, vegetable soup, and mixtures that include vegetables. Although all questions were asked, fried potato consumption and mixtures that include vegetables were not included in the summary scores or analyses. Validity of the FVS compared to true intake ranges from *r*=.66 for men to *r*=.51 for women [35].

For the primary assessment time points for the RCT (baseline, 6, and 24 months), the primary assessment of F&V was the NCI Method [54,55]. This method requires a food frequency assessment such as the NCI FVS and two 24-hour dietary recalls. The recalls were administered over the telephone by the Nutrition Epidemiology core at University of North Carolina, Chapel Hill, using the latest version of the Nutrition Data System for Research (NDSR) software. A nutritionist trained to conduct the telephone recalls used a standard introduction script and a multiple-pass approach interview methodology for the recall. The foods, beverages, preparation methods, amounts, and recipes reported by the participant were entered by an interviewer into the NDSR software to obtain an estimate of nutrient intake. The NDSR 2008 database was used for this study and contained over 18,000 foods, 8000 brand name products, many ethnic foods, supplements, and vitamins. The NDSR calculated food group serving count system was used to assess F&V.

Maintenance of F&V consumption was defined in this study as sustaining a one-serving/day increase in F&V achieved during the acquisition phase. Participants who increased their consumption by more than one serving during the acquisition phase need only maintain a one-serving gain to be considered as achieving maintenance. Maintenance (sustaining at least one serving/day) will be assessed at each time point, separately.

#### Carotenoid Levels

Participants who identified themselves as non-smokers were asked to fast for at least 6 hours prior to the blood draw. Samples were collected at a General Research Center under low light conditions and protected from light throughout processing [38]. The sera were stored at -70 degree C until analysis by a high-performance liquid chromatography method that was used to measure concentrations of alpha-carotene, beta-carotene, lycopene, lutein, zeaxanthin, and beta-cryptoxanthin, by the laboratory at Genox Corporation, Baltimore, MD.

#### Theoretical Constructs

Self-efficacy for F&V consumption was measured using a 6-item scale [56]. Participants were asked how confident they were about eating F&V in six different situations and responded on a 5-point scale: (1 not at all confident) and 5 (completely confident). GST constructs were assessed with a goal assessment battery that included five measures that were designed for this study because no scales existed. The battery included (1) identification of current life goals or priorities, (2) evaluation of success in meeting life goals, (3) evaluation of how current life goals or priorities previously selected conflict or facilitate healthy eating, (4) evaluation of life goal pursuit targeting the top life goal or priority that most interferes with eating a healthy diet, and (5) evaluation of dietary goal pursuit, respectively. First, participants were given a list of 15 life common goals (see Table 3 in Multimedia Appendix 2) and asked to identify those they were currently and actively trying to achieve (“goals or activities that you are spending time and effort on at least weekly”). The goals were ranked by the participants on a scale from 1-10 where 1 is not at all important and 10 is extremely important. Next, participants evaluated their success in meeting the goals by responding to the following question for each life goal: “How successful do you feel in meeting this goal right now?” Participants ranked each goal on a scale from 1-5 where 1 is not successful and 5 is extremely successful. Goal conflict and facilitation were measured by asking how the goals affect success in eating a healthy diet (“does the goal make it easier or harder for you to eat a healthy diet?”). The goal was ranked on a 5-point scale where 1 is much easier and 5 is much harder. An example of a question is “On a scale of 1 to 5, does getting more education or another degree make it easier or harder for you to eat a healthy diet?” Last, the construct of goal pursuit was assessed by asking the participant to evaluate the top life goal or priority that most interferes with eating a healthy diet. Participants selected the one priority or goal that interfered the most with eating a healthy diet, and they were asked to respond to a series of statements about pursing that goal (working toward this goal is exciting for me; I receive a lot of encouragement for working on this goal). Responses were on a scale where “1 is not at all true for me” and “5 describes me very well”. Goal pursuit for healthy eating was assessed last. Participants were asked to rate how well each of 29 statements described them: “I want you to think about the goal of eating a healthy diet. Please think about the goal of eating a healthy diet, and tell me how well each of these statements describes you. Please rate on a 1 to 5 scale where 1 is not at all true for you and 5 means it describes you very well.” Some sample items were “Working toward this goal is exciting”, “I try not to let other goals interfere with this goal”, and “I reward myself for working hard on this goal”.

#### Cost Assessment

Data were collected in order to complete a cost-effectiveness analysis of the maintenance interventions (see Data Analysis section). Direct costs were measured and included the TLC system costs (hardware, software, telephone, and labor). Development costs are excluded. The direct cost of implementing the interventions (TLC) was estimated by tracking the time a research assistant spent on tasks that would occur if the intervention were implemented outside of a research study (ie, labor costs of training personnel and operating and maintaining TLC). All tasks were categorized and tracked on the research assistants’ computers. Time spent on tasks that involved training the participant how to use TLC, telephone calls to assist the participant with TLC and computer server were tracked in a computer program. Research assistants logged onto their research operations system at the start of their workday, and any appropriate tasks were tracked by the system. Tasks that were specific to the research study were not tracked, such as assessment phone calls.

### Sample Size

Sample size for the RCT was based on 80% power to detect a 20% difference in the percentage maintaining an improvement in F&V consumption at 24 months. This sample size also provides 80% power to detect a small-to-medium effect size for differences in mean F&V consumption based on Cohen’s definition [57]. The primary hypothesis was that the treatment groups would maintain their initial gains in F&V consumption better than the control group, and the TLC-GST group would be significantly more successful in achieving this outcome than the TLC-SCT group (ie, GST > SCT > Control). This was tested defining maintenance as sustaining a one-serving increase in F&V that was achieved during the acquisition phase (as this is the eligibility criterion for the RCT). This primary hypothesis was tested using two approaches: a categorical approach and a continuous approach. The categorical hypothesis tests the proportion of the group who maintain, while the continuous tests the differences in F&V serving size. For the categorical hypothesis, the sample size estimation was based on a 20% difference in the proportion of participants meeting the definition of maintenance between groups. If the proportion maintaining gains is 80% in one group, 60% in another, and 40% in a third, there is 80% power of detecting pairwise differences between groups. Expecting 5% attrition at every 6 months from baseline to 24-month time point, a sample size of 405 (n=135 per group) is required at baseline and will yield a final sample of 330 (n=110 per group). This sample size provides 81% power of detecting the difference at 24-month time point between TLC-SCT and Control Groups (60% vs 40%), 87% power of detecting the difference between TLC-GST and TLC-SCT Groups (80% vs 60%), and 99% power of detecting the difference between TLC-GST and Control Groups (80% vs 40%), testing at the two-tailed alpha .05 level. For the continuous hypothesis, group differences are measured by the mean change from baseline to 24-month time point. A sample size of 110 provides 80% power of detecting an effect size of .38 of the standard deviation of the change score in F&V servings.

## Results

### Data Analysis

Data will be analyzed using SAS, version 9.1 for Windows. Alpha level was set at *P*<.05. Descriptive statistics will be used to characterize the different study subject samples before and after the acquisition study period. Descriptive statistics will examine those individuals who were screened for eligibility and those who qualified and enrolled into the RCT. Sample comparisons between those who were eligible and those who were not will be made using data collected at enrollment (screening data). Comparisons of the different study samples will be performed using Student’s *t* test for continuous variables and Pearson’s chi-square test for categorical variables. An additional analysis will be performed evaluating the change in F&V servings from initial screening (enrollment) to baseline (ie, the beginning of the maintenance phase) for the sample who was randomized into the RCT. An intention-to-treat approach using the last observation carried forward approach will be used to include those participants who drop out of the study or for whom there are missing data.

The primary hypotheses for the RCT is that the treatment groups will maintain their initial gains (ie, one-serving increase) in F&V consumption better than the control group, and the TLC-GST group will be significantly more successful in achieving this outcome than the TLC-SCT group (ie, GST > SCT > Control) on both a categorical (primary hypothesis) and a continuous measure (secondary hypothesis) of maintenance at all follow-up time points. The primary time points for the study will be baseline (randomization), 6 months (post intervention period), and 24 months (end of the follow-up period). The primary comparisons will be considered from baseline to 6 months, and baseline to 24 months. Group differences will be compared using a continuous variable (F&V consumption) at these time points. We will also compare groups on the percent who maintained a one-serving/day or greater increase in F&V consumption. The categorical measure of maintenance will be analyzed through multiple logistic regression models, and a continuous measure of maintenance will be analyzed through multiple linear regression models. Independent variables in these models will include a set of indicator variables for study group, baseline levels relating to each outcome variable, and potential confounders (variables found to differ between groups at baseline).

Longitudinal models will be used to explore group differences on dietary indicators over time, using data from all study evaluation points. These analyses will use the Generalized Estimating Equations (GEE) approach to accounting for the longitudinal nature of the data by modeling the within-subject correlation and adjusting both regression parameters and standard errors for this correlation. As compared to traditional repeated measures analysis of variance, the GEE approach allows for the inclusion of all available data from subjects with incomplete follow-up in the analysis. For categorical outcome measures, GEE logistic regression models for longitudinal data will be used, while for continuous outcome measures, GEE linear regression models will be used. Independent variables in these models will include a set of indicator variables for group, a set of indicator variables representing time (with baseline taken as the reference group), and a set of interaction terms modeling differential changes over time for the three study groups. Potential confounders identified in preliminary analyses will also be included in these models. Our primary interest is in the interaction terms, which will test whether the pattern of change in consumption of F&V over time differs by group.

While the primary focus of our analyses of the number of F&V servings is on changes from baseline to 6 to 24 months, our longitudinal models will also allow us to examine maintenance decay in the number of servings from 6 months (at the end of the maintenance intervention) to 24 months. Similarly, our longitudinal models for the categorized maintenance outcome will allow us to examine changes in maintenance from 6 to 24 months as well.

Secondary analyses will examine the influence of psychosocial variables. For TLC-SCT, we hypothesize that the outcomes are mediated by self-efficacy. For TLC-GST, we hypothesize that outcomes are at least partially explained by changes in goal system variables such as levels of inter-goal facilitation, inter-goal substitution, and inter-goal conflict at all major follow-up time points.

These hypotheses will be tested with path analysis. Potential mediational pathways of the effect between the randomized groups and F&V intake for the theoretical construct variables will be examined. Path models will be constructed to test the direct and indirect associations indicated by our research model. Using 6 and 12 month data as indicators of processes of maintenance in both the mid-term (at the end of the maintenance intervention) and in the longer term (6+ months post intervention), path analyses, both separate and combined, will be conducted to examine mediators of maintenance variables as influenced by group assignment. To examine the TLC-SCT change model, paths will be modeled from an intervention variable to self-efficacy to F&V intake. Direct and indirect effects of the intervention will be estimated through standardized path coefficients. For the TLC-GST, goal system variables will be examined in analogous path models.

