## Methods

### Overview

The design for this study includes two phases to examine the maintenance of a dietary behavior change in adults. Figure 1 provides an overview of the study flow and measurement time points. In the first phase (acquisition), an intervention was used to produce a change in F&V consumption in order to study, in a second phase (maintenance), if an intervention targeting maintenance could sustain that change. All interventions were delivered using a fully automated telephony system that used an interactive voice response (IVR) system to generate speech that emulated counseling by a trained behavioral counselor combined with a speech recognition system to understand what the participant said. To perform the study, a sample of healthy adults who consumed less than the recommended level of F&V (ie, ≤ 5 servings/day) were recruited. During the acquisition phase, they were given a tested dietary telephony intervention for up to 6 months, called Telephone-Linked Care (TLC)-EAT, which has been shown in previous studies to have positive effects on initiating dietary improvements, including increased F&V consumption [32,33]. Because both prior studies found an increase of approximately one serving of F&V for the TLC-EAT intervention group, it was hypothesized that this effect would occur in a new sample of participants. F&V intake was examined at enrollment and after 3 months of the acquisition intervention. Participants who increased their consumption of F&V by at least one serving/day became eligible for the second phase (maintenance). Participants who did not show a one-serving increase were allowed to participate for an additional 3 months only. Those who achieved a one-serving increase during the acquisition study were eligible to participate in the second phase (maintenance, randomized controlled trial). Participants who entered the second (maintenance) phase of the study were blinded to the inclusion criterion (eg, an increase of >1 serving/day of F&V). Participants in the maintenance phase were randomized to one of three groups, receiving one of two theoretically based TLC interventions targeting maintenance of behavior (TLC-Maintenance GST or TLC-Maintenance SCT) or to the control group (an assessment only without an intervention). All participants in the randomized controlled trial (RCT) were assessed every 6 months for a total of 2 years post randomization (baseline). The study protocol received full board review and approval by the Boston University School of Medicine Institutional Review Board (NCT00148525). See Multimedia Appendix 1 for the CONSORT-EHEALTH checklist [34].

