### Procedures

The University of Rhode Island Survey Research Center performed study recruitment, assessment, and randomization. The Center randomly selected names from a voter registration list and mailed a letter inviting them to participate in the study. The letter was followed by a phone call from the Center about one week later where the interviewer described the study, screened for eligibility (see Participant section above for eligibility criteria), obtained verbal consent, and administered study instruments. Research assistants at Boston University School of Medicine, where the intervention (ie, TLC-EAT) was hosted, sent participants an enrollment packet in the mail, which contained a welcome letter, consent form for their records, and a manual and personal password for the healthy eating acquisition intervention (ie, TLC-EAT). A week after enrollment, these research assistants called participants to train them on how to use TLC-EAT. Participants did a practice call with the research assistant on the line. Those who completed the training were transferred to the first intervention call (the “training call”) with TLC-EAT. Thereafter, all TLC calls were outbound calls initiated by the automated system, which called participants at the time initially entered into the automated scheduling system during the training call. Participants were asked to complete one TLC-EAT call per week for 12 weeks with the option of rescheduling any of the incoming TLC calls or initiating calls to TLC if preferred. After 12 weeks, F&V consumption was reassessed with the NCI FVS to determine eligibility for the maintenance phase of the trial. Participants who increased by one serving of fruit and/or vegetable were eligible to be randomized to one of three groups for the RCT. Random allocation to group assignment was generated by the SRC’s computer program that used urn randomization protocols to balance groups by gender. Those who did not increase by one serving after 3 months were invited to continue with the acquisition intervention, TLC-EAT, for an additional 3 months and then were assessed again for eligibility into the RCT. Those who qualified and agreed to continue in the RCT were assessed at baseline (randomization), 6, 12, 18 and 24 months post baseline. A random sample of those who qualified for the RCT were invited to complete a blood draw at the university’s General Clinical Research Center at baseline only. Assessments during the RCT included the NCI FVS, 24-hour dietary recalls, and psychosocial measures. Participants received US $20 for completing a survey at baseline, 6-month, 12-month, 18-month, and 24-month time points, and $50 for the in-person, fasting blood draw.

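### LOCF on the primary maintenance outcome scores anyone lost before month 6 as a maintainer on the NCI screener, because the entry criterion and the maintenance criterion are the same one-serving gain

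*Protocol article*

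**What the plan says.** All points are from the protocol article.

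- **Missing data (Data Analysis).** "An intention-to-treat approach using the last observation carried forward approach will be used to include those participants who drop out"; the same sentence covers other missing data. No different rule is given for the primary models.
- **Entry (Overview, Procedures).** "Participants who increased their consumption of F&V by at least one serving/day became eligible for the second phase (maintenance". The instrument is stated: "F&V consumption was reassessed with the NCI FVS to determine eligibility for the maintenance phase of the trial".
- **Outcome (Sample Size; Fruit and Vegetable Intake).** Maintenance is "sustaining a one-serving increase in F&V that was achieved during the acquisition phase (as this is the eligibility criterion for the RCT". For larger gains: "Participants who increased their consumption by more than one serving during the acquisition phase need only maintain a one-serving gain".
- **Analysis (Data Analysis).** The categorical measure is the primary hypothesis and is analysed by logistic regression. The primary comparisons run from baseline to 6 months and from baseline to 24 months.
- **Instrument (Fruit and Vegetable Intake).** At baseline, 6 and 24 months the primary assessment is the NCI Method, which combines the screener with two 24-hour recalls. The screener alone is used at every visit.
- **Attrition (Sample Size).** "Expecting 5% attrition at every 6 months from baseline to 24-month time point", taking 135 per group to 110 per group.

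**The concern.** LOCF assumes that a person's status stays as it was when last seen. In this trial everyone enters having just met the success criterion, and the question is whether that success lasts. For a person with no follow-up value, the rule supplies the favourable answer.

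The plan itself expects relapse. It powers on 80%, 60% and 40% maintaining at 24 months, and it sets out to examine decay between 6 and 24 months. A status carried from an earlier visit is therefore expected to be too good. At stake are the reported maintenance rates in every arm and the differences between arms at both primary time points.

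**Working it through.** **1. The plan's own figures.** Retention is 135 × 0.95⁴ = 109.96 per arm, which matches 110. With n = 110 per arm, two-sided 0.05 and a continuity correction, power is 81.3% for 60% vs 40% and 87.7% for 80% vs 60%, against the stated 81% and 87%. These figures are not in dispute.

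**2. How many values are carried.** Lost before month 6: 135 × 0.05 = 6.75, about 7 per arm. Missing at month 24: 135 − 109.96 = 25.04, about 25 per arm (18.5%).

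**3. Status of a carried baseline.** On the screener it is a success by definition. The alternative criterion in the Discussion (intake at the end of acquisition minus a standard error) is also met by a carried-forward baseline.

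**4. Six months.** The only earlier value in the randomised phase is baseline, so the reported rate is 0.95p + 0.05. If p were 80%, 60% or 40%, the report would be 81%, 62% or 43%.

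**5. Twenty-four months, equal attrition.** Let a be the attrition per interval and p₀…p₄ the maintenance rates at 0, 6, 12, 18 and 24 months, with p₀ = 1 and the same rates in dropouts:

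reported rate = Σₖ₌₀…₃ a(1−a)ᵏpₖ + (1−a)⁴p₄

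At a = 0.05 the weights are 0.05, 0.0475, 0.045125 and 0.042869, and completers have 0.814506. The decay path is an assumption, so three are shown. For a true 40%:

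- All relapse before month 6: 0.05 × 1 + 0.95 × 0.40 = 43.0%.
- Linear (100/85/70/55/40%): 0.050000 + 0.040375 + 0.031588 + 0.023578 + 0.325803 = 47.1%.
- All relapse after month 18: 0.185494 × 1 + 0.814506 × 0.40 = 51.1%.

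| Decay path | True 80% | True 60% | True 40% | 20-point gap becomes |
|---|---|---|---|---|
| Early | 81.0 | 62.0 | 43.0 | 19.0 |
| Linear | 82.4 | 64.8 | 47.1 | 17.6 |
| Late | 83.7 | 67.4 | 51.1 | 16.3 |

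If only NCI Method visits (0, 6 and 24 months) are carried, the linear path gives 83.0/66.1/49.1% and a gap of 17.0 points. This treats every baseline as a success on that measure too. A missing 24-month value is then replaced by one that is 18 to 24 months old.

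**6. Unequal attrition, no true effect.** Both the rates and the path (60/52/46/40% at 6/12/18/24 months) are assumptions. The rejection probability is Φ((δ − 1.96·se₀)/se) + Φ((−δ − 1.96·se₀)/se), with δ the false difference, se₀ the pooled and se the unpooled standard error, and n = 135 per arm.

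- 2% vs 8% per interval, all visits carried: 41.9% vs 47.5%, δ = 5.5 points. With se₀ = 0.0605 and se = 0.0604 the type I error is 14.9%. With NCI Method visits only: 6.5 points, 18.9%.
- 5% vs 10% per interval: 4.5 points and 11.3%; with NCI Method visits only, 5.2 points and 13.6%.

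**The case against.** The strongest reply has four parts.

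- **Instrument.** Eligibility is judged on the screener, but the primary measure at baseline, 6 and 24 months is the NCI Method. The acquisition phase measured intake with the screener alone, so a baseline NCI Method value need not show the gain. This stands. Baseline success is exact on the screener only. If baseline success on the NCI Method were 70% (an assumption), the 2% vs 8% scenario would give 4.7 points and about 12% instead of 6.5 points and 18.9%.
- **Reach.** A reader might infer that every dropout is scored a maintainer. Only about 7 of the 25 per arm are. The other 18 or so carry an observed later status, which is too favourable only if maintenance decays.
- **Size.** A reader might infer that arm differences simply follow dropout rates. The plan assumes equal attrition, under which differences shrink. By the uncorrected two-proportion formula, power for 60% vs 40% is 84.8% with 110 completers per arm. With 135 per arm under LOCF it is 88.3%, 83.5% or 78.1% on the early, linear and late paths. That is modest.
- **Unequal loss.** No unequal rates are given. Outcomes come from telephone surveys by blinded staff, on the same schedule and payment in every arm, so skipping intervention calls is not the same as missing an assessment. The control arm could equally lose more people, which would bias against the interventions.

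Two further readings are not supported. One might see a contradiction with the longitudinal section, where "the GEE approach allows for the inclusion of all available data from subjects with incomplete follow-up in the analysis". Those models are separate and exploratory, and the remark contrasts GEE with repeated-measures analysis of variance. One might also say that LOCF understates standard errors, but this is not shown for the binary outcome: the carried status is a function of observed data, and the problem is bias in what is estimated.

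**Conclusion.** The concern holds in a limited form. On the screener, LOCF makes anyone lost before month 6 a maintainer by construction; on the NCI Method it does so only as far as the two measures agree. Later losses are scored too favourably if maintenance decays, which the plan expects.

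At the planned, equal 5% attrition per 6 months, reported rates are inflated by about 1–4 points at a true 80% and 3–11 points at a true 40%. A true 20-point difference falls to about 16–19 points. These ranges assume the same maintenance in dropouts as in completers and reflect the unknown timing of relapse. The effect is modest under the design as stated.

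A false difference between arms, and the 11–19% type I error, require unequal attrition, which is an assumption here. The rule is still worth replacing: it acts on the primary outcome at both primary time points and presumes success in those with no follow-up.

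**What to change.** Replace the LOCF sentence in Data Analysis as the primary missing-data rule.

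- **Categorical outcome.** Include all randomised participants. Multiply impute continuous fruit and vegetable intake at missing visits, by arm, and derive the maintenance indicator after imputation. Name the instrument imputed and the enrolment reference value from which the gain is computed, since no enrolment NCI Method value exists.
- **Continuous outcome.** Use a likelihood-based mixed model.
- **Sensitivity.** Add an analysis counting missing as not maintained. At the planned retention of 0.8145 this would show true rates of 80/60/40% as 65.2/48.9/32.6%, a clear lower contrast to LOCF. LOCF may stay only as a further sensitivity analysis.

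The cost is a paragraph of wording and some programming, with no new data. Reported maintenance rates will be somewhat lower and intervals possibly wider. The article says that analysis is not complete, so the change can still be made.

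### Covariates for the primary models are picked by chance baseline differences between arms, a rule that will almost never pick gender, the randomisation balancing factor

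*Protocol article*

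**What the plan says.** All references are to the protocol article.

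- **Data Analysis, primary models.** The logistic model (categorical maintenance) and the linear model (continuous measure) contain "a set of indicator variables for study group, baseline levels relating to each outcome variable", plus "potential confounders (variables found to differ between groups at baseline". The hypothesis is tested "on both a categorical (primary hypothesis) and a continuous measure (secondary hypothesis) of maintenance at all follow-up time points", so the logistic model carries the primary hypothesis.
- **Data Analysis, longitudinal models.** These GEE models explore group differences over time. Here too, "Potential confounders identified in preliminary analyses will also be included in these models".
- **Procedures.** Allocation "used urn randomization protocols to balance groups by gender". Gender is not named as a covariate in any model.
- **Fruit and Vegetable Intake.** Maintenance is defined relative to the gain made in the acquisition phase: "Participants who increased their consumption by more than one serving during the acquisition phase need only maintain a one-serving gain". Neither that gain nor enrolment intake is named as a covariate.

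**The concern.** After randomisation, a baseline difference between arms reflects chance. Its size says nothing about whether the variable predicts fruit and vegetable intake two years later. A rule that admits variables because they differ therefore selects on the wrong property, and it does so after the data are in hand.

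Two consequences follow.

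1. **The primary model is not fixed.** For the logistic model this affects more than precision. Adding a prognostic covariate changes which conditional odds ratio is estimated, so the reported effect depends in part on which variables happened to qualify.
2. **The rule works against the design.** The urn scheme pushes gender towards balance, so gender is the variable least likely to differ between arms. If it predicts outcome, omitting it tends to leave standard errors larger than the design earned. The article itself reports that the screener's validity differs by sex (r=.66 in men, .51 in women), so gender plausibly bears on the measured outcome.

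This is a stated rule, not a detail left to a fuller document. An analysis plan that followed the article would inherit it.

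**Working it through.** **1. The plan's own figures.** Inputs from Sample Size: 110 per arm at 24 months, "testing at the two-tailed alpha .05 level", and "If the proportion maintaining gains is 80% in one group, 60% in another, and 40% in a third".

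- Attrition: 405 x 0.95^4 = 329.9, matching the stated 330.
- Two proportions, with the difference reduced by 1/n as a continuity correction. For 60% vs 40%: (0.20 - 1/110 - 1.96 x sqrt(2 x 0.5 x 0.5/110)) / sqrt((0.24 + 0.24)/110) = 0.89, giving power 81.3% (stated 81%). For 80% vs 60% the same formula gives 87.7% (stated 87%).
- Continuous measure: 0.38 x sqrt(110/2) - 1.96 = 0.86, giving power 80.5% (stated 80%).

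The figures reproduce. None of them uses covariates, so they neither support nor refute the point. They are the reference for its size.

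**2. How often chance adds a covariate.** The article attaches no test or threshold to the rule. *Assume* a .05 test on k independent variables. P(at least one enters) = 1 - 0.95^k:

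| k | Chance |
|---|---|
| 5 | 22.6% |
| 10 | 40.1% |
| 20 | 64.2% |

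The article gives no value for k.

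**3. What the rule picks and what it costs.** Simulation with assumed values, 1,500 trials per setting:

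- two arms of 110, gender exactly balanced;
- half of the acquired gain lost on average;
- residual SD 2 servings, gender effect 0.3 or 1.0 serving, treatment effect 0 or 0.9 serving.

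The rule (arm, baseline intake, then gain or gender if different at .05) was compared with a fixed set (arm, baseline intake, gain, gender).

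- Selection: gain entered in about 5% of trials. Gender entered in 0%, which follows from the exact balance assumed. A real urn leaves small imbalances, hence 'almost never' and not 'never'.
- Linear-model standard error, rule vs fixed: 0.279 vs 0.270 (0.279/0.270 = 1.03) with the weak gender effect; 0.287 vs 0.271 (1.06) with the strong one. The rule's standard errors are 3-6% larger.
- Logistic power, rule vs fixed: 71.4% vs 72.7% and 69.3% vs 72.2%, a difference of 1.3 and 2.9 points. Each power has a simulation standard error of about sqrt(0.7 x 0.3/1500) = 1.2 points. Both models were fitted to the same simulated trials, so the differences are more stable than that.
- Rejection with no treatment effect: 3.9-4.7% under the rule and 4.4-5.9% with fixed covariates, all near 5%.

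**4. Upper end.** A second simulation took 60% vs 40%, 110 per arm, and a gain assumed to predict maintenance with log-odds 0.5 to 1.1 per SD. Adjusting for gain raised logistic power from 83.9% to 85.9%, 83.3% to 87.4% and 83.8% to 89.4%, or 2.0, 4.1 and 5.6 points. Its comparator had no baseline term at all, so it is generous to the concern. Together the two simulations span about 1-6 points.

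**5. Continuous measure in general.** If fixed covariates explain an extra share R² of the variance, power is that of 0.38/sqrt(1 - R²):

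| Extra R² | Power | n per arm for 80% |
|---|---|---|
| 0 | 80.5% | 109 |
| 0.05 | 82.4% | 104 |
| 0.10 | 84.4% | 98 |
| 0.20 | 88.3% | 87 |

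The article gives no R², so this is a range and not an estimate.

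**The case against.** The strongest reply is that little is lost. Baseline level is always in the primary models, and baseline intake partly carries the acquired gain, because on the screener it equals enrolment intake plus gain. Type I error stays near 5%. The GEE models are exploratory, where flexible adjustment matters less. All of this stands, and it keeps the point small. It does not rescue the rule, which still fixes the primary model after the data are seen and passes over the balancing factor.

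A reader might also infer more than the article supports:

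- **That the baseline covariate in the logistic model is constant, since everyone randomised had gained a serving.** The wording most naturally means baseline intake, which varies. Eligibility was also judged on the screener alone, while the primary measure is the NCI Method, so qualifying does not fix a participant's status on that measure.
- **That the size of the gain, or needing 3 or 6 months to achieve it, is the strongest predictor of maintenance.** Principal Considerations says it is not known whether larger increases are harder to keep, and nothing in the article says duration is prognostic. A link with gain is plausible from the definition of maintenance, but its strength is assumed.
- **That the plan uses a significance screen.** No test is attached to the rule. The t tests and chi-square tests described nearby compare study samples, such as eligible with ineligible people, and not arms.
- **That gain is excluded.** It is simply not named, and could enter if the arms happened to differ on it.

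**Conclusion.** The point holds as a modest one. The covariate rule for the primary models selects on chance and will almost never admit gender, although the randomisation was restricted on it. The consequences are a primary model, and for the logistic analysis a conditional odds ratio, that depend on the observed data, together with some avoidable imprecision: standard errors about 3-6% larger and logistic power about 1-6 points lower.

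Those sizes rest on assumed prognostic strengths. The 40% and 64% rest on an assumed .05 test and on 10 or 20 independent variables. No bias or excess of false positives has been shown, and the validity of the trial is not in question. The reason to act is that the loss is avoidable at almost no cost, in a trial whose comparison of TLC-SCT with control has a stated power of only 81%. The same wording in the GEE models should follow, with less urgency because those analyses are exploratory.

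**What to change.** 1. In Data Analysis, delete the rule that admits "potential confounders (variables found to differ between groups at baseline" to the primary models, and the sentence "Potential confounders identified in preliminary analyses will also be included in these models" for the GEE models.
2. Prespecify gender and baseline fruit and vegetable intake in servings as covariates in the primary logistic and linear models. Saying servings also removes any doubt about what baseline level means for the categorical outcome.
3. Prespecify gender in the GEE models. Baseline is already one of their time points, so baseline intake need not be added as a covariate.
4. Name one acquisition-phase term, either enrolment screener intake or acquisition gain, because maintenance is defined relative to that gain. One is enough: with baseline screener intake, either determines the other. State that its prognostic strength is an assumption.
5. If wanted, keep adjustment for observed imbalance as a labelled sensitivity analysis.

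The cost is wording only. Every variable is already collected, the article describes the analysis as not yet complete, and the sample size does not change. The covariates should be fixed before any outcome is compared by arm.
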